## Abstract

**Introduction:**

Patients with musculoskeletal conditions often seek care in an emergency department (ED). The problem is that the time required to manage these patients places an additional pressure on ED physician and nursing staff, who are primarily trained and resourced to manage high-acuity patients. Primary-contact physiotherapists could play a greater role in supporting ED physician and nursing staff in the management of patients presenting to the ED with musculoskeletal conditions.

**Methods and analysis:**

The RESHAP-ED trial is a multicentre, pragmatic, open-label, two-arm, parallel randomised controlled trial with nested process and economic evaluations. The trial will investigate whether a primary-contact physiotherapy pathway compared with usual care (primary-contact by physician and/or nursing staff pathway) reduces time spent in ED. Patients with simple musculoskeletal conditions will be recruited from EDs in New South Wales, Australia. The primary outcome is ED length of stay (LOS). Secondary outcomes will include acceptability, feasibility and cost-effectiveness of primary-contact physiotherapy, and explore patients’ and clinicians’ experience. To detect a 30 min between-group difference in ED LOS, 1370 patients will be required. Analyses of the primary and secondary outcomes will be conducted following the intention-to-treat principle. The adjusted mean difference in ED LOS and 95% CI will be calculated using linear regression adjusted for hospital using a random effect model.

**Ethics and dissemination:**

The study received ethical approval from the Sydney Local Health District (RPAH zone) Human Research Ethics Committee (X23-0143). Findings from this study will be disseminated through publication in peer-reviewed journals and conference presentations.

**Trial registration number:**

Australia New Zealand Clinical Trials Registry: ACTRN 12623000782639; Universal Trial Number (UTN): U1111-1292-2883.

STRENGTHS AND LIMITATIONS OF THIS STUDYAs a pragmatic trial, the intervention will be carried out in real-world emergency department (ED) settings, and the results can be immediately applied in routine practice.This is a multicentre trial, including metropolitan and regional EDs, optimising patient recruitment and generalisability of the results.This trial includes nested economic and qualitative evaluations to investigate the cost-effectiveness and acceptability of primary-contact physiotherapy in EDs.As an open-label trial, clinicians and patients will not be blinded to treatment allocation, but trial investigators and statisticians will remain blinded to reduce bias.

## Introduction

### Background and rationale

 Musculoskeletal conditions are common in emergency departments (EDs). In 2022–2023, there were over 432 900 visits for care of a musculoskeletal condition to EDs in Australia.^1^ The time required for musculoskeletal care and discharge planning in the ED places an additional pressure on physician and nursing staff who are primarily trained and resourced to manage high-acuity patients.

‘Primary-contact clinician’ refers to the first healthcare professional who assesses patients in the ED. In EDs, these are usually physician and/or nurse practitioners, even though in the community setting primary-contact care is often delivered by general practitioners (GPs) and allied health professionals, such as physiotherapists, for some of the conditions that people occasionally present with in the ED. Physiotherapists could play a greater role in the initial assessment and management of patients presenting to ED with a musculoskeletal condition. In addition, management and discharge planning, especially for older patients with comorbidities, is time consuming when done well, but can be delegated to an ED primary-contact physiotherapist, who is trained to work within an advanced practice physiotherapy model of care.

Preliminary evidence suggests that timely access to physiotherapy in EDs reduces waiting time, overall ED length of stay (LOS) and is well received by physician and nurse staff.^2 3^ For instance, evidence from observational data suggests that a primary-contact physiotherapy service in EDs may reduce patient waiting time by half and may reduce ED LOS by approximately 30–80 min compared with patients seeing other healthcare providers.^4^,^6^ Relying solely on physician and nurse practitioners can result in people with musculoskeletal conditions waiting longer in EDs as these clinicians have to prioritise more urgent patients. A systematic review recently published by our group reported that there are only five randomised trials in this area, and none has measured the impact of primary-contact physiotherapy on ED patient flow or ED LOS.^7^ Currently, there is one ongoing cluster randomised controlled trial conducted in Canada comparing the effectiveness of an advanced practice physiotherapist-led model of care with usual ED physician care.^8^ Although primary-contact physiotherapists have been working in Australian EDs for approximately 20 years and are considered a standard care pathway in many hospitals, there is a great deal of variation in physiotherapist involvement in the ED setting.^9^,^11^ This may be because high-level evidence of clinical and cost-effectiveness of primary-contact physiotherapy care in EDs is lacking.^12 13^

We are proposing a randomised trial to compare two approaches, both standard of care in Australia, to the assessment and management of patients who present to ED with simple musculoskeletal conditions. The more common care pathway (control group in this study) is that patients are first seen by a physician and/or nurse practitioner for assessment and management and may subsequently be referred to a physiotherapist. A less common, but well-established care pathway (intervention group in this study) involves initial assessment and management by a primary-contact physiotherapist.

### Hypothesis

Our hypothesis is that a primary-contact physiotherapy pathway in the ED to primarily assess and manage patients presenting with musculoskeletal conditions will reduce ED LOS, provide comparable health service outcomes and satisfaction with care, and be cost-effective and acceptable to patients and clinicians.

### Objectives

The RESHAP-ED trial aims to determine the clinical effectiveness, cost-effectiveness and acceptability of a primary-contact physiotherapy pathway compared with usual care (where patients are primarily managed by physician and/or nurse practitioners) for patients with musculoskeletal conditions presenting to EDs.

### Primary objective

The primary objective of this trial is to determine if a primary-contact physiotherapy pathway reduces ED LOS. The primary objective of the RESHAP-ED trial addresses the important issue of patient flow in EDs.

### Secondary objectives

The secondary objectives of the trial are to (1) investigate key health service outcomes (eg, duration of clinical care, re-presentation rates), (2) explore patient-reported outcomes (ie, pain, quality of life, satisfaction with care, adverse events), (3) determine cost-effectiveness and (4) conduct process evaluation to understand the acceptability and feasibility of the primary-contact physiotherapy pathway in ED.

## Methods and analysis

### Study design and registration

The RESHAP-ED trial is a pragmatic, multicentre, open-label, two-arm, parallel randomised controlled trial with nested process and economic evaluations. The trial protocol has been reported according to the Standard Protocol Items: Recommendations for Interventional Trials statement guidelines.^14^ The completed randomised trial and its results will be reported according to the Consolidated Standards of Reporting Trials and the Consolidated Health Economic Evaluation Reporting Standards 2022 statements.^15 16^ This study received ethical approval from the Sydney Local health District (SLHD) HREC (RPAH zone, reference number X21-0143, 13 June 2023), and the trial was prospectively registered with the Australian and New Zealand Clinical Trial Registry (ANZCTR: 12623000782639).

### Study setting

The trial will be conducted in the EDs of three metropolitan hospitals (Royal Prince Alfred, Sutherland and Ryde Hospitals), and two regional hospitals (Gosford and Wyong Hospitals) in New South Wales, Australia.

### Participants

All consecutive patients who present with a musculoskeletal condition to the participating EDs during the time the primary-contact physiotherapists are on shift will be screened by the physiotherapists for eligibility.

To be included in the trial, patients must fulfil all the following inclusion criteria: (1) adult patient 18 years or older; (2) present with a simple musculoskeletal condition. This would include, but is not limited to, soft tissue injuries (joint, ligament, tendon or muscle pain), musculoskeletal neck and low back pain, closed peripheral fractures not requiring reduction or orthopaedic fixation (indicated from triage notes), spontaneously reduced joint dislocations; and (3) have a triage score of either 3 (urgent), 4 (semi-urgent) or 5 (non-urgent) as per the Australasian Triage Scale (ATS). Patients with a triage score of 2 will also be included when presenting with an isolated joint dislocation, including shoulder, digit, patella or temporomandibular joint (indicated by triage notes).^17^

Patients will be excluded if presenting with at least one of the following exclusion criteria: (1) already assessed by a physician and/or a nurse practitioner in the ED as indicated on the electronic Medical Record (eMR); (2) any non-musculoskeletal/non-orthopaedic condition, such as open wounds, eye problems, foreign bodies and poisonings; (3) presentations outside the primary-contact physiotherapists’ working hours; (4) the triage notes indicate soft tissue injuries that may require surgical intervention; (5) the triage notes indicate a fracture requiring reduction and/or surgical fixation; (6) the triage notes indicate signs or symptoms of serious pathology (eg, spinal fracture, cauda equina syndrome, malignancy, infection or inflammatory origin of pain); (7) comorbidities requiring immediate emergency care (eg, cardiac, respiratory; or psychiatric issues as indicated on the triage note); (8) patient is unable to provide sufficient informed consent to participate (eg, cognitive impairment, intoxication, unable to understand spoken or written English) and (9) re-presentation of a patient who has already been included in the trial.

### Patient selection and recruitment

Every person presenting to the ED with a musculoskeletal condition will be triaged by nursing staff and be recorded in the ED’s electronic patient list (Cerner FirstNet^®^). This triage process will not constitute a formal clinical assessment by a healthcare provider, such as a nurse practitioner. Throughout their shift, the physiotherapists will review the ED’s electronic patient list to identify potentially eligible patients. This is a normal practice for physiotherapists within EDs in Australia. For each patient where the visit reason in the triage notes suggests a musculoskeletal condition appropriate for primary-contact physiotherapy management, the physiotherapist will fill out an electronic eligibility form in the Research Electronic Data Capture (REDCap) database. If the patient is found to be eligible during the initial screening, the physiotherapist will inform the patient about the trial and provide the trial information flyer. A waiver of consent for screening and randomisation was granted by the Ethics Committee as this study is testing the effectiveness of two standard of care pathways on ED patient flow. Flow of participants is presented in figure 1.

**Figure 1 F1:**
[figure not shown]
Flow of participants through the study. ED, emergency department; REDCap, Research Electronic Data Capture.

### Randomisation

All patients who fulfil the eligibility criteria will be randomised into the trial by the physiotherapist using REDCap. A 1:1 randomisation allocation sequence, incorporating randomly permuted block sizes of 2 and 4, and stratification by hospital site, will be generated prior to the commencement of the trial by an independent statistician not involved in participant recruitment, treatment, follow-up or statistical analysis using Statistical Analysis System (SAS) software. The randomisation schedule will be uploaded into REDCap to allow the randomisation to be performed online by the physiotherapist. Patients will be randomly allocated to either the primary-contact physiotherapy group (intervention group) or to the medical and/or nurse practitioner group (control group). REDCap will allocate each patient a participant ID number.

### Blinding

Due to the nature of the intervention, complete blinding will not be possible. Patients and clinicians will not be blinded to group allocation. The researcher downloading the eMR data, including primary outcome, will be blinded to group allocation. The statistician analysing the data and the investigators interpreting the results will also be blinded. The group allocation will be revealed to all investigators once the analyses are completed, and results are validated using randomly scrambled group allocations.

### Trial clinicians

Trial clinicians included in the RESHAP-ED trial will be ED primary-contact clinical staff, such as physicians, nurses and physiotherapists, who routinely manage patients presenting to EDs with a primary complaint of a musculoskeletal condition. For each ED site, at least one primary-contact physiotherapist (level 4) will be employed to be responsible for the patient enrolment process and the primary-contact physiotherapy pathway assessment and management. The research team will be responsible for the training of all ED staff working in the trial to make sure the trial procedures are followed as per study protocol and the Australian Code for the Responsible Conduct of Research, 2018.^18^

### Trial intervention and control

#### Primary-contact physiotherapy group (intervention group)

Following randomisation, patients who are allocated to the primary-contact physiotherapy group will be flagged in the eMR system. Recording who provides initial care in the system is a standard procedure in Australian EDs.

The physiotherapy intervention will be delivered by a senior physiotherapist (level 4 in Australia), a highly experienced clinician responsible for advanced patient assessment and management. As primary-contact clinician, they can independently diagnose and treat patients. In Australian EDs, a primary-contact physiotherapist is authorised to refer patients for diagnostic imaging and specialist consultations, with some jurisdictions also permitting them to prescribe a limited range of medications. Following an initial assessment, the primary-contact physiotherapist will choose the best course of management in consultation with the patient. In this trial, management of patients presenting with symptoms of low back pain will be provided following recommendations from the Australian Low Back Pain Clinical Care Standard.^19^ For any other musculoskeletal condition presentation, the clinical care will be guided by the best practice advice recommended by the NSW Emergency Care Institute.^20^

The primary-contact physiotherapist may consult an ED physician and/or nurse practitioner (collaborative model of care) or autonomously manage the clinical care of patients. In the autonomous model of care, the physiotherapist is the primary-contact clinician responsible for the patient assessment, management, diagnosis and discharge with no involvement of a physician and/or nurse practitioner. In the collaborative model of care, after selecting and assessing the patient, the primary-contact physiotherapist shares management and discharge decision-making with a physician and/or nurse practitioner.

In this trial, all patients will be provided with a discharge plan, including timely follow-up in the outpatient setting. Outpatient care will be provided by existing outpatient services such as outpatient physiotherapy, virtual hospitals, GP clinics, or specialist clinics, if required.

#### Primary-contact physician and/or nurse practitioner group (control group)

The control group will consist of primary-contact clinical care delivered by an ED physician and/or nurse practitioner in line with normal practice at the site. Patients allocated to the control group will not be seen by the primary-contact physiotherapist and will wait to be seen by a primary-contact physician and/or nurse practitioner. Physician and/or nurse practitioners may refer patients to see a physiotherapist in the ED as secondary-contact or may refer patients to the outpatient physiotherapy department following discharge (collaborative model of care).

### Data collection and study follow-ups

#### Data collection procedures

Health service outcomes and patient demographic characteristics will be extracted directly from the hospital eMR. Patient-reported outcomes will be collected via an online survey, supplemented by telephone calls. At days 1, 7 and 42 following randomisation, participants will receive a text message including a link for the e-Consent Form and online survey. One reminder message will be sent to non-responders at each follow-up time point. If no response is received, a trial research officer will contact them via telephone to complete the assessment.

#### Data management and monitoring

Research data from online surveys will be stored into REDCap; data from hospital eMR will be stored in password-protected folders on the University of Sydney server. A master code sheet will enable the data extracted directly from the hospital eMR to be reidentified via the patients’ medical record number to allow for data validation and audit as required, but only available to the trial coordinating principal investigator. The data will be scrutinised for omissions and errors and will be archived on the University of Sydney server for 15 years, after which data will be deleted.

### Outcome measures

#### Primary outcome

The primary outcome for this trial will be ED LOS; defined as the period between when a patient presents at an ED, and when that patient is discharged from the ED.

#### Secondary outcomes

##### Health service outcomes

Time to clinical care; defined as time elapsed in minutes for each patient from ED presentation to the commencement of ED (non-admitted) clinical care.Duration of clinical care; defined as the period between when clinical care commences and the end of the (non-admitted) patient ED clinical care.Proportion of patients whose ED LOS is ≤4 hours (ie, proportion with care completed within 4 hours).Proportion of patients ‘seen on time’; defined as the proportion of presentations for which the waiting time to commencement of clinical care was within the benchmark time specified in the definition of the ATS category.^21^Proportion of patients admitted to the ED Short Stay Unit.Proportion of patients admitted to hospital inpatient units.Proportion of patients who received imaging.Proportion of patients who received opioids.Proportion of patients who received gabapentinoids.Proportion of patients who received specialist consult within the ED.Proportion of patients referred to specialist clinic.Proportion of patients re-presenting to the ED for the same chief complaint within 72 hours of discharge.Proportion of patients readmitted to the hospital inpatient units for the same chief complaint within 30 days of index inpatient admission.

##### Patient-report outcomes

Average pain intensity measured using the numeric rating scale ranging from 0 (no pain) to 10 (worst imaginable pain). This outcome will be measured at days 1, 7 and 42 following ED discharge.Quality of life measured using the EuroQol 5-Dimension 5-Level (EQ-5D-5L).^22 23^ This outcome will be measured at days 1, 7 and 42 following ED discharge.Satisfaction with ED care measured using item 31 of the ED Patient Experience of Care survey advocated by the American College of Emergency Medicine.^24^ This outcome will be measured at day 1 following ED discharge.Adverse events will be assessed on day 1 following ED discharge. Participants will complete an online survey that will include a question prompting participants to report the occurrence of any adverse event during the ED stay. Participants experiencing an adverse event will have the opportunity to include more information about the adverse event. The investigators will review the clinical notes of participants reporting adverse events and extract adverse event data. The Medical Dictionary for Regulatory Activities will be used to code adverse event data. A blinded independent assessor will review adverse event data and assign attribution to study interventions.

The trial’s schedule of assessment is presented in table 1.

**Table 1 T1:** Trial schedule of assessment

Procedures	Day 0 (emergency department visit)	Day 1	Day 7	Day 42
Patients screened for inclusion/exclusion criteria	✓			
Participants given trial flyer	✓			
Participants randomised via Research Electronic Data Capture	✓			
Interventions—physiotherapy or physician/nurse pathway	✓			
Participants invited by physiotherapist to qualitative interviews	✓			
SMS invite to online questionnaire and e-Consent		✓		
Online questionnaire completion—pain intensity, EuroQol 5-Dimension 5-Level		✓	✓	✓
Online questionnaire completion—satisfaction with care, adverse events		✓		
Completion of qualitative interviews	Patient’s interview—completed between day 1 and day 42 post emergency department discharge following randomisation.Clinician’s interview—completed after 50 patients are randomised at a participating site.			

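### Investigator blinding, as stated, is not delivered for adverse-event extraction: investigators read clinical notes that would ordinarily reveal the pathway

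*Protocol article*

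**What the plan says.** Four parts of the Protocol article bear on this.

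- **Strengths and limitations box (after the registration number).** The open-label design is disclosed and then qualified: "clinicians and patients will not be blinded to treatment allocation, but trial investigators and statisticians will remain blinded to reduce bias". Nothing limits this to investigators with a particular role.
- **Blinding.** "Patients and clinicians will not be blinded to group allocation". Then: "The researcher downloading the eMR data, including primary outcome, will be blinded to group allocation". And: "The statistician analysing the data and the investigators interpreting the results will also be blinded". The section ends by saying that no investigator learns the allocation until the analyses have been completed and the results validated on scrambled allocations.
- **Primary-contact physiotherapy group.** After randomisation, "patients who are allocated to the primary-contact physiotherapy group will be flagged in the eMR system". The same paragraph says that recording which clinician gives initial care is routine in Australian EDs.
- **Patient-report outcomes (adverse events).** Participants are asked in the day 1 survey whether anything adverse happened during the ED stay. For those who say yes, "The investigators will review the clinical notes of participants reporting adverse events and extract adverse event data". Finally, "A blinded independent assessor will review adverse event data and assign attribution to study interventions".

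**The concern.** The two arms differ in who makes first contact: a senior physiotherapist, or a physician and/or nurse practitioner. A clinical note from the visit is written by, and about the work of, those people. Anyone who reads it to find out what went wrong will usually see who saw the patient first, even before reaching the eMR flag. The article assigns that reading to the investigators while telling readers that investigators are blinded.

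Extraction from free-text notes involves judgement about what is recorded as an event and how it is described. The trial has a directional hypothesis: shorter stay with otherwise comparable outcomes. Adverse events are a named secondary outcome that speaks to the comparable-outcomes part. If the person extracting knows the arm, events could be recorded differently by arm. The later attribution by a blinded assessor cannot correct that, because the assessor works from what was extracted. Readers would also credit the trial with a protection that this step does not have.

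**Working it through.** No figure in the plan bears on this point, so the check sets the sections side by side.

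1. **Who is said to be blinded, and until when?** The strengths box covers trial investigators in general. The Blinding section first names only those interpreting the results, but its closing statement on disclosure covers all investigators and places it after the analyses. Two of the three statements are therefore unrestricted.

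2. **Does the note review fall inside that period?** Yes. Adverse events have to be extracted and coded before they can be analysed, and disclosure follows the analyses. Timing does not resolve the conflict.

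3. **Do the notes reveal the arm?** Intervention patients carry a flag in the eMR, and the first clinician is recorded there. The control-group section says that control patients are not seen by the primary-contact physiotherapist and wait for a physician or nurse practitioner. Both professions can still appear in either arm: the physiotherapist may share care with a physician or nurse practitioner, and a control patient may be referred to a physiotherapist in the ED as a secondary contact. The order of contact, or the flag, would ordinarily still identify the pathway. This is an inference from how the arms are defined, and it need not hold for every record.

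4. **Is there a stated safeguard?** None for this step. No redaction is described, and the note reviewers are not said to be different people from the blinded interpreters. The master code sheet under Data management and monitoring controls re-identification of extracted data; it does not control what a reader of the notes sees.

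5. **The eMR downloader.** The flag and first-clinician record are in the source system, but a download can leave fields out, and the article does not list the fields taken. The adverse-event note review is not assigned to this person. Result: a possible risk, not a contradiction.

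6. **The assessor.** This person is described as blinded and independent and receives adverse event data. No section gives them the notes, the eMR or the allocation. Attributing events to the study interventions is awkward to do masked when the intervention is the profession of the clinician, but relatedness to the ED care received can be judged without the arm. Result: again a possible risk.

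7. **Another route.** Under Process evaluation, patient interviewees come only from the physiotherapy arm and are contacted by the research team. Team members who do this learn the arm of those patients. The article does not say whether they are among the blinded investigators.

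**The case against.** The strongest defence is that the Blinding section describes as blinded only the investigators who interpret results, so other investigators may read notes without breaking any promise. That reading is possible, but the article never states the separation, and both the strengths box and the disclosure statement are wider. The defence therefore shows how the text could be repaired rather than that it is already consistent.

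A second defence is that a condensed article leaves operational detail to the full protocol. That holds for the list of downloaded fields and for how the assessor's material is prepared, so neither is treated as an error here. It does not cover the investigator limb, where the article makes a positive claim and also describes a procedure that defeats it.

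A third is that adverse events come to light through self-report by participants who know their arm, before any note is opened. This is correct: masking the reviewers would not remove that bias. It is a separate and disclosed limitation, however, and it does not justify leaving a second, avoidable one in place.

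Several stronger readings are tempting, but the documents do not support them:

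- **That the downloader and the assessor are also unblinded.** No section shows either of them the allocation.
- **That the blind is lost in essentially every reviewed case.** Mixed care in both arms means this is not demonstrated.
- **That adverse events are the main safety comparison.** The article does not call them that; they sit among the patient-reported outcomes to be explored.
- **That judging whether a re-presentation or readmission is for the same chief complaint is unmasked.** The article does not say how this is determined, and a visit reason is recorded at triage, before randomisation.

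**Conclusion.** The point stands in a limited form. Investigator blinding, as claimed in the strengths box and in the disclosure statement of the Blinding section, is not delivered for adverse-event extraction. The exposure covers participants who report an adverse event in the day 1 survey, and within that group the step of deciding what to take from the notes. It may extend to coding, since the article does not say who codes. The number of such participants and the direction and size of any bias cannot be derived from the article.

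The conclusion rests on two assumptions: that ED notes ordinarily show who made first contact, and that no unpublished masking step or separation of roles is in place. If the full protocol has either safeguard, only the wording of the article needs correcting. The primary analysis is little affected, because ED length of stay comes from routinely recorded times and the analyses are programmed on scrambled allocations. The matter should be corrected, but it does not threaten the trial's main conclusion.

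**What to change.** 1. Move the note review from the investigators to existing trial staff who do not interpret results, for example the trial research officer who already telephones survey non-responders. They extract the adverse event data and remove clinician profession and the eMR flag before a case goes to the assessor.
2. Have the assessor judge relatedness to the ED care received, on the masked narrative, with the arm merged afterwards.
3. If this is not adopted, or where investigators have already reviewed notes (recruitment began on 22 November 2023), limit the claims in the strengths box and the Blinding section to investigators who interpret results and do not review notes.
4. Confirm that the flag and first-clinician fields are left out of the outcome download and of the assessor's material. If they already are, one sentence is enough.

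The cost is protocol or procedure wording plus a little redaction time, confined to participants who report an event. No change to sample size, endpoints or staffing is needed. The drawback is that some masked narratives lose context, which may make relatedness harder to judge in a few cases.
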